## Abstract

**Background:**

Screening, brief intervention, and referral to treatment for adolescents (SBIRT-A) is widely recommended to promote detection and early intervention for alcohol and other drug (AOD) use in pediatric primary care. Existing SBIRT-A procedures rely almost exclusively on adolescents alone, despite the recognition of caregivers as critical protective factors in adolescent development and AOD use. Moreover, controlled SBIRT-A studies conducted in primary care have yielded inconsistent findings about implementation feasibility and effects on AOD outcomes and overall developmental functioning. There is urgent need to investigate the value of systematically incorporating caregivers in SBIRT-A procedures.

**Objective:**

This randomized effectiveness trial will advance research and scope on SBIRT-A in primary care by conducting a head-to-head test of 2 conceptually grounded, evidence-informed approaches: a standard adolescent-only approach (SBIRT-A-Standard) versus a more expansive family-based approach (SBIRT-A-Family). The SBIRT-A-Family approach enhances the procedures of the SBIRT-A-Standard approach by screening for AOD risk with both adolescents and caregivers; leveraging multidomain, multireporter AOD risk and protection data to inform case identification and risk categorization; and directly involving caregivers in brief intervention and referral to treatment activities.

**Methods:**

The study will include 2300 adolescents (aged 12-17 y) and their caregivers attending 1 of 3 hospital-affiliated pediatric settings serving diverse patient populations in major urban areas. Study recruitment, screening, randomization, and all SBIRT-A activities will occur during a single pediatric visit. SBIRT-A procedures will be delivered digitally on handheld tablets using patient-facing and provider-facing programming. Primary outcomes (AOD use, co-occurring behavior problems, and parent-adolescent communication about AOD use) and secondary outcomes (adolescent quality of life, adolescent risk factors, and therapy attendance) will be assessed at screening and initial assessment and 3-, 6-, 9-, and 12-month follow-ups. The study is well powered to conduct all planned main and moderator (age, sex, race, ethnicity, and youth AOD risk status) analyses.

**Results:**

This study will be conducted over a 5-year period. Provider training was initiated in year 1 (December 2023). Participant recruitment and follow-up data collection began in year 2 (March 2024). We expect the results from this study to be published in early 2027.

**Conclusions:**

SBIRT-A is widely endorsed but currently underused in pediatric primary care settings, and questions remain about optimal approaches and overall effectiveness. In particular, referral to treatment procedures in primary care remains virtually untested among youth. In addition, whereas research strongly supports involving families in interventions for adolescent AOD, SBIRT-A effectiveness trial testing approaches that actively engage family members in primary care are absent. This trial is designed to help fill these research gaps to inform the critical health decision of whether and how to include caregivers in SBIRT-A activities conducted in pediatric primary care.

**Trial Registration:**

ClinicalTrials.gov NCT05964010; https://www.clinicaltrials.gov/study/NCT05964010

**International Registered Report Identifier (IRRID):**

PRR1-10.2196/54486

## Introduction

### Alcohol and Other Drug Use Problems Exert Enormous Negative Impacts on Adolescents

The level of unmet intervention need among adolescents with risky alcohol and other drug (AOD) use is a persistent public health problem. Recent data from the 2023 Monitoring the Future national survey indicate that, among 12th graders, 46% reported using alcohol (more than just a few sips); 39% marijuana; 39% nicotine via vaping; and 43% illicit drugs, including inhalants [1]. According to the 2023 National Survey on Drug Use and Health (NSDUH), among adolescents aged 12 to 17 years in 2022, 8.7% (or 2,228,000 adolescents) reported a substance use disorder in the past year [2]. Troublingly, the rates of treatment enrollment among this high-need age group are considerably low, with only 4.6% of the adolescents who meet the criteria for substance use disorders receiving specialty care [2]. When left unaddressed or ineffectively treated, AOD use during adolescence often continues into adulthood, precipitating long-term substance use and mental health disorders and being associated with a cascade of other health consequences, as well as imparting enormous economic costs to society [3].

Preventing youth AOD use and intervening early with those who use are key to reducing the many consequences of risky use. As shown in neurodevelopment research on risky behavior in youth, adolescence is the critical period both for starting AOD use and experiencing harmful consequences as a result [4]. Adolescence is a developmental stage characterized by risk behaviors, including AOD experimentation; adolescents are also vulnerable to negative impacts of addictive substances, which can further impair judgment, interfere with brain development, and increase addiction risk [5]. Moreover, AOD use is associated with the 3 leading causes of death among teenagers: motor vehicle crashes, homicides, and suicides [6]. Prevention and early intervention can also prevent progression to more severe AOD use that carries the risk of overdose and death.

### Screening, Brief Intervention, and Referral to Treatment for Adolescents Is Widely Recommended for Addressing AOD Use in Primary Care

Given that the majority of teenagers in the United States visit primary care (PC) clinics at least once per year [7], PC settings provide rich opportunities to detect and intervene with adolescents at risk for AOD problems. The most recent guidelines issued by the American Academy of Pediatrics prescribe universal AOD screening for teenagers during both routine preventive appointments and nonpreventive PC visits [8]. Recognizing the unique role that PC providers can play in meeting the challenge of adolescent AOD use, the American Academy of Pediatrics further recommends that providers learn procedures for screening, brief intervention, and referral to treatment (SBIRT) and how to integrate SBIRT into medical care for adolescents [9]. SBIRT for adolescents (SBIRT-A) entails a set of clinical procedures for detecting youth at risk of AOD problems and delivering appropriate prevention or early intervention, including universal screening for AOD risk level and formulaic guidelines for providing brief motivational interventions and appropriate treatment referral to patients identified as at risk [8,10]. Notably, when delivered using standard procedures, SBIRT-A amounts to an adolescent-focused approach in which most or all activities involve only the given youth [11,12].

SBIRT-A is widely recommended to promote detection and early intervention for AOD use in PC [9,13]. In practice, although 50% to 86% of pediatricians report screening for AOD use, the use of standardized screening assessments and systematic brief interventions (BIs) is low [14]. In research trials, approximately 25% to 35% of adolescents screen positive for substance use when systematic screening is implemented [15,16]. Research reviews and meta-analyses show that BI procedures can be effective in reducing adolescent drinking [17,18] and, when delivered in PC settings, have demonstrable impacts and cost-effectiveness for quality-of-life indicators [18-20]. Recent studies, including 2 multisite effectiveness trials that collectively examined thousands of adolescent visits in PC clinics [15,21], further suggest that SBIRT-A is scalable in PC [16,22].

Despite these promising developments, there remain significant limitations in SBIRT-A research and practice in PC. Prior controlled SBIRT-A studies conducted in PC have yielded inconsistent findings with regard to implementation feasibility [23], in large part due to significant practice barriers to delivering SBIRT-A in pediatric care. PC providers are generally reluctant to implement SBIRT-A, citing insufficient time, limited training in substance use, unfamiliarity with the procedures, a lack of readiness to address a positive AOD screen result, limited resources for referrals to specialty care, and concerns about confidentiality [24-28]. Moreover, despite data from systematic reviews supporting BIs in PC [18], the US Preventive Services Task Force recently determined that evidence is insufficient to assess the balance of benefits versus harms of screening adolescents for unhealthy AOD use due to variability in study methods and quality [29]; consequently, it withheld a recommendation for widespread SBIRT-A delivery in pediatric settings [10,30]. Given existing gaps in the SBIRT-A research base on the effectiveness of SBI and the effect of involving caregivers in SBI procedures as well as the impact of BIs on outcomes beyond AOD use and the corresponding uncertainties in the policy and practice status of SBIRT-A in pediatric settings, there is urgent need to advance the scope of SBIRT-A effectiveness studies in PC [28].

### Tablet-Guided SBIRT-A Procedures Have the Potential to Reduce Implementation Barriers

Tablet-guided SBIRT-A approaches have the potential to reduce documented implementation barriers through offering a standardized road map for addressing AOD use. Tablet-guided SBIRT-A procedures eliminate the need for the memorization of complicated adjunctive SBIRT-A procedures. Instead, tablet-guided SBIRT-A approaches provide a new and systematic way to address positive AOD screening that is more efficient than the existing eclectic practices that providers currently rely on. Providers are guided through step-by-step interventions designed with their time constraints in mind, leveraging automated tools and well-vetted workflow integration [16,31,32]. Procedures include recommendations for providers on addressing positive AOD screens with youth and their caregivers without jeopardizing youth autonomy or violating confidentiality.

### Incorporating Caregivers in SBIRT-A Procedures Has the Potential to Enhance Effectiveness

#### Overview

The standard SBIRT-A approach focuses almost exclusively on the adolescent patient by including only the given youth in screening and intervention procedures [11]. Nevertheless, the SBIRT-A evidence base indicates a need for improvements in effectiveness and feasibility in PC [33,34]. Incorporating caregivers in SBIRT-A activities could enhance the effectiveness of the approach in several ways, as outlined in the following subsections.

#### Broaden the Screening Search

The “no missed opportunities” paradigm [35] recognizes caregivers as vital sources of information about adolescent AOD risk. Using multiple sources of information to assess youth AOD use is more accurate than relying on any single source [36]. Studies suggest that caregiver reports are fair to good proxy measures of youth AOD behavior [37], although they typically underestimate consumption [38]. Caregiver report may be particularly useful when youth have minimized self-report of AOD use or impairment. Involving caregivers in screening has the potential to boost the accuracy of problem identification and also set the stage for their involvement in BI and referral to treatment (RT) procedures [39].

#### Widen the Screening Net

In addition to assessing AOD use, screening procedures can collect supplemental data to generate a multidomain profile of AOD risk. The screening net can be widened in at least 2 ways. First, caregivers can complete screening tools for youth co-occurring behavior problems that both signal and exacerbate AOD risk: anxiety and depression, impulsivity and sensation seeking, and aggression and conduct problems [4,40]. Second, caregivers as well as youth can provide valuable data on family strengths, including key protective factors such as parent-adolescent communication about AOD use [41,42]. Data on these supplemental risk and protective factors can be converted into “risk algorithms” that more accurately codify AOD risk profiles, boosting both the acuity of risk screening and the attunement of subsequent SBIRT-A activities [43].

#### Deepen BI Impact

Developmental science asserts that supportive familial networks are potent protections against individual-level developmental processes that predispose adolescents to AOD and other risky behavior. BIs for adolescent AOD use that incorporate caregivers have shown their mettle [44] and are likely to have considerable added value over adolescent-only BIs in PC settings [45], especially given that caregivers who harbor AOD and related behavioral concerns for their children often seek anticipatory guidance from PC providers [27].

#### Strengthen RT Linkages

Influencing teenagers seeking medical care to enroll in AOD services typically requires caregiver involvement [39]. Nevertheless, there are numerous challenges to engaging caregivers in treatment referral, including caregiver skepticism about the value of AOD services, the stigma and fear of being judged for the youth’s problems, and hopelessness about the possibility of change [46]. PC providers are well positioned to shape caregiver attitudes and behaviors concerning treatment referral, given their authority on health care issues. Providers can explain AOD risks and ramifications, acknowledge past efforts to address AOD and related behaviors, and reinforce the importance of caregiver influence on adolescent well-being along with the possibility of behavior change—techniques common to family-focused treatment engagement models [47]. Providers can also join caregivers in talking directly with their teenagers about AOD risk, using evidence-based strategies [48] to mobilize caregiver capacity to facilitate youth enrolling in AOD services.

### Specific Aims of the Randomized Effectiveness Trial

This randomized effectiveness trial will advance research on SBIRT-A in PC by conducting a head-to-head test of 2 conceptually grounded, evidence-informed approaches: a standard adolescent-only approach (SBIRT-A-Standard) versus a more expansive family-based approach (SBIRT-A-Family). The SBIRT-A-Family approach enhances the procedures of the SBIRT-A-Standard approach by screening for AOD risk with both adolescents and caregivers; leveraging multidomain, multireporter AOD risk and protection data to inform case identification and risk categorization; and directly involving caregivers in BI and RT activities [43]. The trial will test the effectiveness of SBIRT-A-Standard versus SBIRT-A-Family for preventing the escalation of AOD use (aim 1); reducing AOD use risk factors and consequences, decreasing co-occurring behavior problems, enhancing parent-adolescent communication about AOD use, and increasing quality-of-life indicators (aim 2); linking youth and families to behavior counseling services (aim 3); and investigating the extent to which the effects of SBIRT-A-Family vary based on youth characteristics (age, sex, and race or ethnicity) and youth AOD risk status (aim 4).

## Methods

### Trial Design

This trial uses a 2-arm parallel-group multisite randomized effectiveness design. The 2 SBIRT-A approaches (SBIRT-A-Standard and SBIRT-A-Family) both use digitally supported BIs [16,49] that are a substantial upgrade over routine practice and consistent with the recommendations of the American Academy of Pediatrics to leverage digital tools. Individual youth and their caregivers are randomized as a family unit to the study condition. Adolescent and family outcomes for 2300 youth (n=2000, 86.96% identified as at risk of AOD use and n=300, 13.04% as a developmental comparison identified as low risk) are assessed over 1-year follow-up.

The protocol was developed according to the SPIRIT (Standard Protocol Items: Recommendations for Interventional Trials) 2013 statement (Multimedia Appendix 1).

### Study Participants

#### Study Sites and Providers

The study occurs in 3 hospital-affiliated pediatric settings: Mass General for Children, Boston Medical Center, and Columbia University Irving Medical Center. All 3 settings are in major urban areas that serve a diverse range of patients. In aggregate, these 3 settings receive approximately 20,000 visits annually from youth in the targeted age range (12-17 y); the sites reported that 10% to 15% of age-targeted youth routinely identify as positive for AOD use via existing site screening methods. All sites currently screen youth routinely for AOD risk via digital screening methods and expressed intention to adopt BIs. All site staff (eg, physicians, nurse practitioners, and behavioral specialists) who provide BI and RT services to adolescents are eligible to provide SBIRT-A services as part of this trial. Physicians in leadership roles at each site (eg, the medical director) will serve as site champions to pioneer the implementation of site-based study procedures and promote acceptance and buy-in among all site staff [50]. Each site will receive performance feedback (eg, the uptake of SBIRT procedures and progress toward patient enrollment goals) and participate in cross-site monthly learning collaboratives to discuss and problem-solve implementation barriers and facilitators. The study team will partner with participating providers to revise implementation procedures as needed to enhance the uptake of SBIRT procedures.

#### Study Patients and Inclusion Criteria

The study enrolls adolescents and their caregivers attending a PC visit at 1 of the 3 study sites. The study inclusion criteria are as follows: youth aged 12 to 17 years; a primary caregiver (ie, parental figure) also in attendance; youth is fluent in English, and caregiver is fluent in English or Spanish; both are capable of using audio-assisted informed consent procedures and independently operating a handheld tablet; and both complete routine site AOD risk screening questions prompted during PC visit intake. On the basis of existing patient flow at each site, we have projected aggregate self-reported demographic characteristics of enrolled youth (Table 1).

This profile supports planned moderator analyses for sex, race, ethnicity, and age subgroups. The randomization procedures will (1) block and stratify by clinic site and (2) use imbalance minimization procedures for adolescent age (12-14 y vs 15-17 y) and study clinician.

**Table 1 table1:** Projected aggregate self-reported demographic characteristics of enrolled youth (N=2000).

Demographic characteristics			Participants, n (%)
**Sex**			
	Male	1000 (50)	
	Female	1000 (50)	
**Race and ethnicity**			
	Black	620 (31)	
	Latinx	580 (29)	
	White	680 (34)	
	Other	120 (6)	
**Age**			
	12 to 14 years	1100 (55)	
	15 to 17 years	900 (45)	

### Recruitment, Randomization, Intervention Flow, and Outcome Assessment Procedures

Study recruitment and randomization as well as all SBIRT-A activities occur on the day of the visit in PC offices. Figure 1 depicts the flow of patient recruitment, patient randomization, and SBIRT-A delivery for various risk categories. Recruitment efforts will be multimethod, consisting of (1) informational flyers in wait areas, (2) outreach to families by site research staff, and (3) warm handoff by site administrators and providers when needed. Interested caregivers are prompted to contact on-site research staff, who then give the designated caregiver a tablet to (1) complete an electronic research consent form, (2) provide family demographic and brief assessment information, and (3) complete a screening tool assessing their concerns about the adolescent’s AOD use and related behavior problems as well as family communication about AOD issues. Simultaneously, research staff give a tablet to the youth, who completes an electronic research assent form, and if their caregiver gives consent, an AOD screening tool and brief assessment information.

For families in which both caregiver and youth give informed consent and assent and complete screening, the tablet automatically (1) randomizes the family to study condition, using urn randomization to achieve balanced allocation of participants based on sex, race, ethnicity, and age group; and (2) computes a risk category. In SBIRT-A-Standard, the risk category (*low risk*, *riding risk only*, *distant use*, or *recent use*) is assigned using youth screening data only, while SBIRT-A-Family uses youth plus caregiver screening data to assign the risk category (*low risk*, *hidden substance use risk*, *named mental health risk*, or *named substance use risk*). For youth and families assigned to the *low risk* category (ie, no positive screen result), youth are invited to view tablet-delivered psychoeducation slides, and caregivers are invited to view a video tour and enrollment link to web-based educational and support resources for adolescent AOD. For youth and families assigned to an *at risk* category, youth and caregivers each view tablet-delivered psychoeducation videos and (for some risk categories) complete provider-facing BI and RT activities that are differentiated based on condition assignment and tailored to the respective risk categories. Multimedia Appendix 2 summarizes study activities for each condition; full descriptions are provided in the Study Conditions subsection. All study providers are trained to deliver both SBIRT-A approaches (ie, provider crossover design).

Every adolescent or family assigned to an *at risk* category in either condition is enrolled until study capacity is reached (n=2000). In addition, a randomly selected subsample of adolescents (n=300; balanced across conditions) screened as *low risk* are followed for outcome assessments; the selection of the group categorized as *low risk* uses quota sampling based on sex, race, ethnicity, and age. Outcome data are collected via remote digital assessment methods at initial assessment (as soon as possible after the PC visit) and at 3, 6, 9, and 12 months after the PC visit using REDCap Cloud software (Research Electronic Data Capture developed at Vanderbilt University and licensed to cloud-based technology company nPhase, Inc), a widely used secure, Health Insurance Portability and Accountability Act (HIPAA)–compliant, web-based data collection platform. Figure 2 shows the SPIRIT (Standard Protocol Items: Recommendations for Interventional Trials) checklist depicting the schedule of trial enrollment, interventions, and assessments. All youth and caregivers separately receive both email and SMS text prompts when assessments are due, using contact information provided during the consenting process. When either youth or caregiver fails to complete a follow-up assessment, research staff members blinded to condition assignment reach out to arrange a live assessment via telephone or videoconference. Each assessment requires approximately 20 minutes to complete.

Clinicians and families enrolled in the study retain the right to withdraw consent at any time. The protocol will be discontinued at any site where procedures become burdensome or otherwise impinge on the routine performance of participating staff. Analysis of intervention impacts and potential harm will be continuous throughout the trial. In cooperation with the administration of the partnering sites, investigators will provide full study debriefing and offer counseling referrals to any participant aggrieved or injured due to trial participation.

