### SBIRT-A-Standard Procedures

#### Screening (Approximately 2 Min)

All consented youth aged 12 to 17 years complete the CRAFFT (car, relax, alone, forget, friends, trouble) screening tool [54,55], which assesses the number of days during the past year and then the past 3 months during which various formulations of AOD were used, as well as whether they have ridden in a car whose driver was intoxicated; youth who respond negatively to all questions are categorized as *low risk*. If youth report >0 days of AOD use, the tool asks 5 additional questions assessing use risk and consequences; in addition, youth who report nicotine use in the past 30 days complete a nicotine dependence measure, the Hooked on Nicotine Checklist [56], modified to include nicotine vaping. Screening data are then used to sort youth into 3 risk categories: *riding risk only* (no reported AOD use but indicated rode in car driven by intoxicated person), *distant use* (reported AOD use in past year but not past 3 months), or *recent use* (reported AOD use in past 3 months). All screening data are summarized in a tablet-delivered clinician report to guide provider-facing intervention activities.

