### SBIRT-A-Family Procedures

#### Screening (Approximately 2 Min Apiece)

Screening procedures incorporate CRAFFT procedures for youth described for the SBIRT-A-Standard condition. They also incorporate two sources of caregiver-report data: (1) an assessment of caregiver beliefs about their child’s AOD use and worries about the impact of AOD use, and (2) a well-validated checklist of youth mental health problems [67] that yields clinical cut scores for 4 domains. If both youth and caregiver report no AOD use or clinically elevated mental health problem, the family is categorized as *low risk*. Otherwise, screening data are combined to sort families into 3 risk categories: *hidden substance use risk* (youth reports AOD use in past year; caregiver reports no youth AOD use in past year), *named mental health risk* (caregiver reports no youth AOD use in past year; caregiver reports clinical-level score for at least 1 youth mental health domain), and *named substance use risk* (caregiver reports youth AOD use in past year with or without reporting a clinically elevated mental health score). Adolescent and caregiver screening data are both summarized in the clinician report to guide provider-facing intervention activities.

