**(1)**

**(2)**

wherein (1) and (2) are jointly estimated submodels for the SBIRT-A-Standard and SBIRT-A-Family conditions, respectively. The dependent variable in each equation is the log odds (*logit*) that AOD use response *Y* for person *i* at time point *j* (*j*=1 to 5) is in category *c* (*c*=1 to *C*−1) or lower where *c* is one of the ordinal response categories created from the AOD measure. The *b*_0_*_i_* parameters in (1) and (2) are random intercepts estimating the log odds of *Y_ij_*≤*c* at initial assessment in each condition; the *b*_1_ parameters estimate the linear rate of change (ie, slope) in the log odds of *Y_ij_*≤*c* across measurement points, which are indexed by the variable *TIME_j_*. The *γ_c_* parameter estimates thresholds between adjacent categories on the given AOD variable. The intercept in each submodel is specified as a random effect to account for the nesting of repeated measurements within individuals. Slope parameters are specified as fixed effects. The model is specified as jointly estimated simultaneous equations for each study condition, rather than a single model containing an intervention main effect and interaction term, to allow for greater flexibility in modeling group-specific effects as well as for comparing each condition to the normative comparison (NC) group of youth (in which the given youth, standard condition or youth and family, family condition, screened negative). Changes in the levels of AOD use are captured by the *b*_1_ parameters in each submodel, where positive values of *b*_1_ indicate an increase in the log odds of being in a lower AOD use category on each logit over time compared to the initial assessment. The causal effect of assignment to SBIRT-A-Standard versus SBIRT-A-Family on AOD use (ie, the intent-to-treat effect) is estimated as the difference between *b*_1_*_,sbi−fam_* and *b*_1_*_,sbi_*_._ Separate models are fitted for each AOD use outcome variable. To account for nonindependence due to the clustering of individuals within clinic sites, indicator variables controlling for the fixed effect of each clinic will be included as covariates in submodels (1) and (2) [95].

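### Entry to the followed at-risk cohort is decided after randomisation by a different rule in each arm, so the Aim 1–3 contrasts are not the intent-to-treat effects claimed; the size and direction of any bias are unknown

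*Protocol article*

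**What the plan says.** All places are in the protocol article.

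- **Order of steps** (Recruitment, Randomization, Intervention Flow, and Outcome Assessment Procedures). Once caregiver and youth have both completed screening, the tablet first "randomizes the family to study condition, using urn randomization to achieve balanced allocation of participants based on sex, race, ethnicity, and age group", and then computes the risk category.
- **Rule by arm** (same section). In Standard the category "is assigned using youth screening data only, while SBIRT-A-Family uses youth plus caregiver screening data to assign the risk category".
- **Who is followed** (same section). Every family in an at-risk "category in either condition is enrolled until study capacity is reached (n=2000"). Low-risk families are followed only through "a randomly selected subsample of adolescents (n=300; balanced across conditions) screened as" low risk.
- **At risk in Standard** (SBIRT-A-Standard Procedures, Screening). Recent use, distant use, or riding risk only, the last defined as "no reported AOD use but indicated rode in car driven by intoxicated person".
- **At risk in Family** (SBIRT-A-Family Procedures, Screening). Youth-reported use, caregiver-reported use, or the mental health category: "caregiver reports no youth AOD use in past year; caregiver reports clinical-level score for at least 1 youth mental health domain". The low-risk rule there looks at AOD use and mental health and does not mention riding.
- **Estimand** (Aim 1 Analyses). "The causal effect of assignment to SBIRT-A-Standard versus SBIRT-A-Family on AOD use (ie, the intent-to-treat effect) is estimated as the difference between" the two slopes. The normative comparison (NC) group is also defined by arm: youth negative in Standard, youth and family negative in Family.
- **Power** (Study Power). Both arms start at 62.3% with no alcohol use.

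**The concern.** Randomisation protects a comparison of everyone randomised, or of a subset chosen in the same way in both arms. Here the screening data precede randomisation, but the rule applied to them depends on the arm. Two kinds of youth are fully followed in one arm only:

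| Youth screen | Caregiver screen | Standard | Family |
|---|---|---|---|
| Past-year use | any | at risk | at risk |
| Negative | reports use, or clinical-level score | low risk | at risk |
| Riding only | clear | at risk | low risk |

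Only the first row is common to both cohorts whatever the caregiver says. The cohorts can therefore differ at the start and in their natural course. Youth who begin as non-users can only stay or move up in use, whereas users can move down, so comparing slopes does not remove the problem. Aim 2 (which includes behaviour problems, one of the domains used to select youth in Family) and Aim 3 (counselling) compare the same cohorts. The 12-month comparisons with the NC group use levels and carry any level difference directly.

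**Working it through.** **1. The plan's own figure.** 2000 × 0.80 = 1600, or 800 per arm. Testing 67.9% against 78.4%: SE = √(0.679×0.321/800 + 0.784×0.216/800) = 0.0220. Then 0.105/0.0220 = 4.77, and Φ(4.77 - 1.96) = 0.997. The stated 0.99 reproduces with this simplified test. From the common start of 62.3%, the planned log-odds changes are logit(0.784) - logit(0.623) = 0.787 and logit(0.679) - logit(0.623) = 0.247, a difference of +0.54. All of this presumes exchangeable cohorts.

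**2. Model with no treatment effect.** Let a, r and m be the shares of screened youth who report use, are riding-only with a clear caregiver screen, and are flagged by the caregiver only.

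- *From the document:* 62.3% to 67.9% in Standard; 10% of non-users start within a year (the NC group is expected to fall from 100% to about 90%); a = 10–15% (site-reported positives, Study Sites and Providers).
- *Assumed, because no figure is given:* r = 2–8%; m = 5–20%; riding-only and caregiver-only youth are non-users at the start; initiation and cessation are the same in both arms.
- *Cessation c, set to reproduce Standard:* 0.679 = 0.9×0.623 + c×0.377, so c = 0.314.
- *Users with no alcohol use at the start:* u = [0.623(a + r) - r]/a.
- *Family at the start:* F0 = (a·u + m)/(a + m).
- *Family at 12 months:* F12 = 0.9·F0 + 0.314(1 - F0).

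Middle case, a = 0.125, r = 0.05, m = 0.15: a·u = 0.623×0.175 - 0.05 = 0.0590; F0 = 0.2090/0.275 = 76.0%; F12 = 0.684 + 0.075 = 75.9%. Of 2000, Standard has 2000×0.175/0.450 = 778 and Family 1222.

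| a, r, m | Family start → 12 months | 12-month difference (points) | Difference in log-odds change |
|---|---|---|---|
| 0.10, 0.08, 0.05 | 54.8% → 63.5% | -4.4 | +0.12 |
| 0.125, 0.05, 0.05 | 62.3% → 67.9% | 0 | 0 |
| 0.125, 0.05, 0.15 | 76.0% → 75.9% | +8.0 | -0.25 |
| 0.10, 0.02, 0.20 | 84.9% → 81.2% | +13.3 | -0.52 |

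The first and last rows are the extremes of the assumed grid. Where bias exists, its sign is opposite on the two scales.

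**3. Sensitivity.** Raising a to 30% (the article's Introduction gives 25–35% positive under systematic screening) with r = 5% and m = 10% gives +2.8 points and -0.08. At a = 12.5% and r = 5%, if 20% of caregiver-only positives in fact use, m = 10% gives about 0 and m = 15% gives +1.6 points, against +4.9 and +8.0 if none do.

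**4. False-positive rate, with other inputs.** Simulation of 1600 youth at five time points with correlation 0.90, using a per-person slope test as a stand-in for the ordinal mixed model. Assumed: 20% users and 5% riding-only, 80% of the latter caregiver-clear. With one common rule: 4.6% (slope) and 4.9% (12-month level). With arm-specific rules: near nominal at m = 4%, where the groups cancel; 38% and 48% at m = 10%; 80% and 84% at m = 15%.

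**The case against.** *Wider detection is part of the Family strategy.* True. But the effect of that strategy is then defined over all randomised families, which needs follow-up of all of them or a properly weighted sample. The plan compares the at-risk cohorts and places the 300 low-risk youth in a separate reference group. Site indicators and imputation for dropout do not address selection into the cohort.

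*Riding-only handling in Family may be less settled than it looks.* The recruitment section glosses low risk as no positive screen result, Family uses the same CRAFFT, and Figure 1 and Multimedia Appendix 2 are not shown. This stands as a caveat on one row of the table. If riding-only youth were followed in both arms, the caregiver-only mismatch would remain and the excess of non-users in Family would grow.

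*The size is assumption-driven.* This stands in full. Several stronger readings are tempting, and the document supports none of them:

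- A reader might infer a false gain for Family. Direction depends on unreported prevalences, and whenever the 12-month level favours Family in this model, the Aim 1 slope contrast runs against it.
- A reader might infer that regression to the mean is bound to distort the behaviour-problem outcome. Selection uses the screening score, while modelling starts at the later initial assessment, so much of the regression may precede time zero. It is possible, not shown.
- A reader might put a figure on the Aim 3 distortion. No counselling rates are given.
- Unequal arm sizes might be read as bias. They only cost precision: 700:1300 is worth 2×700×1300/2000 = 910 per arm instead of 1000.

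**Conclusion.** Wrong as written. On the document's own rules, assignment decides who belongs to the analysed cohort. The Aim 1–3 contrasts between the at-risk cohorts are therefore not intent-to-treat effects, the equal 62.3% start is not secured, and the NC group has the same fault. This conclusion needs no prevalence assumption.

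The amount of bias does. With users at 10–15%, riding-only at 2–8%, caregiver-only at 5–20% and no treatment effect, it spans about -4 to +13 points at 12 months and about +0.12 to -0.52 on the Aim 1 scale. It vanishes when r = m and shrinks if user prevalence is higher or some caregiver-only positives do use. At one end it could nearly offset the planned slope effect of +0.54; at the other it modestly inflates it. Aim 3 and the behaviour-problem outcome are exposed by an unknown amount. Chance cancellation is not a basis for a causal claim.

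**What to change.** 1. Make the primary between-arm comparison the youth who report past-year AOD use on the screening CRAFFT. They are at risk and followed in both arms (distant or recent use in Standard; an at-risk category in Family whatever the caregiver reports), and the report precedes randomisation. This is an analysis change only and covers families already enrolled.
2. By amendment, for future enrolment, let the tablet set follow-up and NC membership by one arm-blind rule computed from the two screens. The caregiver tool, which covers "AOD use and related behavior problems as well as family communication about AOD issues", is already completed in both arms before randomisation. The arm-specific category would then steer only the intervention.
3. Report the arm-specific at-risk cohorts as descriptive, not as intent-to-treat.

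**Cost.** The primary set is smaller: in the middle case 2000×0.25/0.45 ≈ 1110, about 890 after 20% loss. That exceeds the 560 for which the article claims power of 0.95, but the claim does not carry over, because the users' starting proportion differs (0.0590/0.125 = 47% in the middle case, not 62.3%). Power must be re-simulated and restated. The set omits riding-only and caregiver-only families, so it does not test the wider-detection part of the Family strategy. Step 2 needs no new screening data, but some follow-up slots go to families now reached only through the sample of 300. Recruitment began in March 2024, and discordant families not followed since then mostly cannot be recovered, so the amendment should be prompt.
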